| 1. **Objectives, Specific Aims and Rationale**   *Objective*  To investigate the use of antibiotics and their protective effect against complications of infection to inform the development of risk prediction models to guide antibiotic treatment decisions for suspected infection in primary care.  *Aims*   1. Estimate the incidence of i) GP consultations for infection and ii) antibiotic prescriptions by: age-group, gender, SES, ethnicity, selected co-morbidities, obesity and smoking status 2. Describe antibiotic prescribing patterns linked to the reason for the prescription by: age-group, gender, SES, ethnicity, selected co-morbidities, obesity and smoking status 3. Estimate the incidence of adverse outcomes in the following 28 days including: hospital admission for infection; A&E admission; re-consultation for infection; re-consultation for antibiotic side-effects (rash, nausea, …) and death for patients with a GP consultation for i) respiratory tract infection ii) urinary tract iii) skin/soft tissue infection, comparing patients with each listed age/co-morbidity group (including smoking status and obesity) to non-comorbid patients 4. Estimate the number of patients needed to treat with antibiotics to avoid one infection-related adverse outcome, comparing the results for each age/co-morbidity group to non-comorbid patients 5. Develop risk prediction tools to support clinical decision making and communication with patients   *Rational*  We have previously shown that more than half of all antibiotic prescriptions in primary care are issued to less than 10% of patients, and that this 10% of patients have high levels of co-morbidity.1 Targeting such high-frequency users of antibiotics in antimicrobial stewardship programmes might provide opportunities for a more effective intervention approach. Underlying this hypothesis is the assumption that it might be safe and feasible to reduce prescribing in patients with the highest levels of antibiotic prescribing, many of whom have co-morbidity.  To investigate whether higher rates of antibiotic use are likely to be justified in higher risk patients compared to patients who lack these risk factors, we will undertake a series of studies to investigate which patients in terms of age, gender, SES, ethnicity, selected co-morbidities, obesity and smoking get the most antibiotics. We will determine which patients are most likely to receive antibiotics for which infections and relate this to national guidance on antibiotic prescribing. To estimate whether the protective effect of antibiotics differs according to the patient’s age and the presence of co-morbidity, obesity or their smoking status, we will estimate the risk of infection related adverse-outcomes, comparing patients who have been treated with antibiotics to those who have not been treated with antibiotics for each of these groups. We will use these estimates to calculate the number of patients who need to be treated with antibiotics to avoid one infection-related adverse outcome (NNT), accounting for age, gender, SES, ethnicity, co-morbidity, obesity and smoking status. This will inform the development and validation of individualised risk-prediction models to support clinical decision-making and patient communication around the need for antibiotic treatment for suspected infection in primary care. |

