| 1. **Study Background**   Over the past 70 years antibiotics have revolutionised how we practice medicine, underpinning routine surgery through to cancer therapies and organ transplantation. Unfortunately, most antibiotics have a finite lifespan as drug resistant strains emerge; an inevitable consequence of bacterial evolution.  Resistance to antibiotics is largely driven by the inappropriate use and overuse of these drugs in humans and animals. Although the majority of highly drug resistant infections emerge in hospitals, 75% of antibiotics for human use are prescribed in primary care.2 The most common reasons for prescription of an antibiotic in primary care are for the treatment of respiratory tract, urinary tract, and skin and soft tissue infections. Despite guidelines on the management of these infections,3 large variations exist in the rates of antibiotic prescribing between individual practices in the UK4–6, with some practices prescribing at twice the rate compared to other sites.  Significant efforts have been made to understand the factors that influence the GP’s decision to prescribe an antibiotic.7 Examples of interventions that have been developed to reduce antibiotic use include symptom-based scoring systems or point-of-care diagnostics to improve diagnostic certainty.8 There have also been a range of initiatives to improve communication between the doctor and patient, to reduce unnecessary antibiotic use.9 The main tool currently used in primary care is the Treat Antibiotics Responsibly Guidance Education Tools (TARGET) toolkit, which was designed by Public Health England.10 It aims to influence prescribers’ and patients’ personal attitudes, social norms and perceived barriers to optimal antibiotic use.  To date, these interventions have targeted all patients who consult for an infection in primary care, despite the fact that some patients are never or rarely prescribed antibiotics, whereas others may have many courses of antibiotics in a single year. This patient-level variation in antibiotic prescribing is likely to be driven by a combination of demographic, behavioural and clinical factors including the presence of co-morbidity. For example, higher rates of antibiotic prescribing might be justified in patients with COPD for the treatment of bacterial infective exacerbations.6 By contrast, for conditions such as obesity, where there is also evidence that patients are more likely to be prescribed antibiotics,1 the clinical indication for increased antibiotic use is less clear.  We speculate that reductions in antibiotic resistance may require targeted public health interventions aimed at reducing antibiotic prescribing for patients who have the highest frequency antibiotic use. To test whether it might be safe and feasible to reduce antibiotic prescribing to patients with co-morbidity in clinical practice (who account for a substantial burden of total antibiotic use), we estimate the protective effect of antibiotic treatment against infection-related adverse outcomes, comparing effects in patients with co-morbidity to those in controls without co-morbidity. Based on this, there is then a need to develop tools enabling a better understanding of risk to support clinical decisions about which patients need antibiotics and communication with patients. |

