| 1. **Study Type**   First we will **describe** the incidence of and relationships between antibiotic prescribing, GP consultation for infection and infection related adverse outcomes for all patients and for subgroups of patients based on risk factors including: age, gender, SES, co-morbidity, smoking status and obesity.  Next we will then **test the hypothesis** that the protective effect of antibiotics against adverse outcomes of infection differs between groups of patients with and without these risk factors.  Finally, we will use our results to inform the **methodological** development of risk prediction models to support clinical decisions around antibiotic treatment. |

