| 1. **Data/ Statistical Analysis**   *1. Estimate the incidence of i) GP consultations for infection and ii) antibiotic prescriptions*  For every patient in cohort 1, data on all consultations for infection and antibiotic prescriptions occurring within the study period will be extracted. We will estimate the incidence of GP consultations for infection and antibiotic prescriptions. This will be done for all consultations and prescriptions, and then separately for each category of infection and each class of antibiotics, based on chapter 5.1 of the British National Formulary (BNF) (see Appendix Tables 1 & 2). The denominator will be estimated as total person-time contributed by patients in the cohort during the study period. We will use Poisson regression to estimate the adjusted rate of consultation and prescription, taking account of the effect of age, gender, SES, ethnicity, selected co-morbidity, smoking and obesity. Random effects will be included to take account of clustering of observations by practice. Rates will be assessed for overdispersion by additionally fitting a negative binomial model and testing for alpha greater than zero via a likelihood-ratio test. If rates are found to be overdispersed, the negative binomial model will be used instead of a Poisson model. Adjusted rate ratios will be presented with 95%-confidence intervals.  *2. Describe antibiotic prescribing patterns linked to the reason for prescription*  The overall number of antibiotic prescribing episodes will be calculated for each patient individually, counting all recorded prescriptions between 1st April 2007 and 31st December 2015. For each episode, a clinical indication will be ascertained. Read codes for a diagnosis or symptom of infection recorded on the same day as the antibiotic prescription will be assumed to represent an indication for the prescription. Where more than one possible indication within the same type of infection is recorded on the day of prescription, the more granular code will be used. If multiple indications across different types of infection are recorded, the prescription will be labelled as having multiple indications. Conversely, if no infectious indication for a prescription was found, the prescription will be labelled as having no infectious indication and we will look for any non-infectious codes associated with the date of antibiotic prescription. The ten most common indications will be established and compared to the same numbers for the period from 1998-2001.14 This approach will be replicated for each class of antibiotics based on chapter 5.1 of the BNF. Patterns of repeat consultation or prescription during episodes of infection which may be prolonged will be investigated for each antibiotic prescription extracted in objective 1. We will define a new episode as a consultation or prescription recorded at least 28 days after any previous consultation for infection or antibiotic prescription. We will undertake sensitivity analyses to investigate the impact of using different time periods to define an episode. We will also examine the use of regular (prophylactic) antibiotic treatment.  Proportions and appropriate 95%-confidence intervals will be calculated and all results will be stratified by age-group, gender, SES, ethnicity, selected co-morbidity, obesity and smoking status. Descriptive data will be displayed graphically.  *3. Estimate the incidence of adverse outcomes in the following 28 days*  For each of the selected clinical infection syndromes in the nested cohort study, events in CPRD, HES and ONS will be searched for all adverse outcomes of interest (see *M.* Exposures, Health Outcomes§ and Covariates). Crude incidence rates of for each outcome will be calculated for patients who were treated (exposed) and not treated (unexposed) with an antibiotic. The denominator will be estimated as the total person-time contributed by patients at risk of each adverse outcome, taking account of the fact that this will be different for each outcome. For example, exposed and unexposed patients cannot consult General Practice if they have been admitted to hospital and should therefore not contribute to the denominator during this period when estimating rates of GP re-consultation in the 28 days following consultation for infection. A Poisson regression model will be used to estimate adjusted rates of adverse outcomes in each group, controlling for age, gender, socio-economic status, ethnicity, co-morbidity, obesity and smoking status and assessing for interaction between age and co-morbidity. Random effects will be included to take account of clustering of observations by practice. If the outcomes are overdispersed, negative binomial models will be used instead of Poisson models. Adjusted rate ratios will be presented with 95%-confidence intervals.  *4. Estimate the number of patients needed to treat with antibiotics to avoid one infection-related adverse outcome*  For each clinical infection syndrome-related adverse outcome identified in objective 3, the odds of that outcome in the 28 days following consultation for those treated with antibiotics (unexposed) and not treated with antibiotics (exposed) will be estimated using logistic regression. We will calculate adjusted odds ratios for the protective effect of antibiotics, adjusting for age, gender, SES, ethnicity, year/season, co-morbidity and the probability of receiving antibiotic treatment (see *O. Plan for addressing confounding*) and assessing for interactions with age and co-morbidity. We will use mixed models to adjust for clustering at a practice level and to take account of clustering of observations within a patient due to repeat episodes of infection. Where there is a significant effect of antibiotics between treated and untreated patients, the NNT or NNH to prevent one individual from developing an adverse outcome is calculated as *1/(absolute risk difference)*. A significant effect will be defined by a p-value < 0.05 for the coefficients of antibiotic treatment and its interactions. To avoid an arbitrary cut-off point, p-values close to 0.05 will also be assessed but discussed separately. The NNT will then be used to assess the clinical relevance of any significant differences found. Whilst the relative risk reduction (RRR) may be similar, the NNT may be different due to differing background risk. This will be explored.  *5. Develop risk prediction tools to support clinical decision making*  For each cohort (i.e. for each of the clinical syndromes of UTI, RTI and SSTI), we will develop a logistic regression risk model to predict the risk of adverse outcomes if patients are treated versus not treated with antibiotics. Models will be developed on a random sample of 80% of the observations within a cohort, reserving 20% of the data to estimate the model’s predictive performance.  A negative outcome will be defined as the occurrence of any of the following within 28 days following the index consultation: hospital admission for infection or complication; re-consultation for infection; A&E admission; death. Antibiotic treatment will be defined as a prescription of an antibiotic on the day of consultation for clinical syndrome. Risk factors will be selected based on the analyses outlined in objectives 1-4 and broadly grouped into: socio-demographic variables, co-morbidity and clinical presentation. Biologically plausible interactions between risk factors and age and between risk factors and co-morbidities will be examined.  Whereas age and sex will be forced into the model, other risk factors will be added in order of their significance in objective 4. Risk factors will be kept in the model if they improve the predictive performance of the model as defined by model discrimination and model calibration.17 For example, a risk factor will be used in the model if it improves discrimination and/or calibration. If a variable improves discrimination but reduces calibration, it will still be included in the model, but will be omitted if it increases calibration at the cost of discrimination.  Model discrimination, i.e. the model’s ability to correctly identify patients with and without an outcome, will be estimated using the concordance (c) statistic.18 The c statistic represents the probability that between two randomly chosen patients, one with the outcome and one without, the model assigns a higher score to the patient with the outcome. As a second measure, model calibration will be assessed using the Hosmer-Lemeshow test.18 We will additionally assess model calibration graphically for reasons for poor calibration by comparing the mean observed outcome in deciles of predicted risk. In this calibration plot, the intercept indicates the extent to which predictions are systematically too low or too high, while the slope reflects overfitting of the model.  For each model, we will estimate the internal validity of discrimination and calibration estimates using cross-validation with bootstrap subsampling based on 1000 iterations. In a secondary analysis, we will assess model performance in subgroups by age, sex and co-morbidity.  Finally, we will develop a simplified scoring system using the risk factors in the model,17 assigning the total score to a specific absolute risk of adverse outcomes in the 28 days following consultation, comparing outcomes if an individual is treated versus not treated with antibiotics. We will assess the predictive performance of the risk scores using the approaches outlined above. |

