| 1. **Plan for addressing confounding**   In objectives 1-3 the aim is to describe rates and undertake descriptive analyses rather than to make inferences about the effect of antibiotic treatment, which is the purpose of objectives 4 and 5. For this reason the issue of confounding is only relevant to objectives 4 and 5.  Individuals who are at higher risk of complications will be more likely to be prescribed antibiotics by their GP (i.e. confounding by indication), introducing a systematic difference between those who are treated and not treated with antibiotics. In this scenario, untreated cases will be less likely to experience adverse events irrespective of their exposure to antibiotics, tending to underestimate the protective effect of antibiotics. We will use propensity score methods to attempt to adjust for this issue. These methods are increasingly used to mitigate the consequences of non-random allocation of treatment in observational studies by modelling the a priori probability of each patient to receive the treatment.  We will use the treatment propensity scores to perform an inverse probability of treatment weighting to account for baseline differences in treated and untreated participants. This will enable assessment of absolute risk and numbers needed to treat to prevent re-consultation and hospitalisation in different groups.19 Propensity score weighting in effect produces a synthetic sample in which the distribution of measured baseline covariates is independent of treatment assignment. Presentation and analyses of results are very similar to a randomized trial allowing assessment of absolute risk and numbers needed to treat in different groups.  In order to create appropriate propensity scores, we will attempt to capture indicators for severity of disease and patients’ risk of complication, such as prior hospitalisation and immunosuppression. Measures such as vital signs are usually poorly recorded which can hamper efforts to estimate disease severity. To overcome this issue we will use GP prescribing preference as an instrumental variables, as described by Davies et al 2013.20  Besides confounding by indication, a number of further factors might influence prescribing. The decision to prescribe an antibiotic is a complex process, depending on multiple characteristics on the patient and practice level. Patients’ demographic factors, patients’ attitude towards antibiotic prescribing, physicians’ workload, date of consultation and geographic location of the practice have been found to influence physicians’ prescribing decisions.21 The use of further instrumental variables may help to estimate the impact of these factors in our analysis and we will also control for differences in prescribing habits between practices through the application of random effects models taking account of potential correlation within multiple episodes of the same patient and between patients within the same practice.  Acknowledging that differences in practice prescribing do not necessarily constitute actually differing prescribing habits but might instead reflect underlying differences in coding, we will undertake an exploratory analysis to look at variation between practices graphically. Using a novel approach we will visualise variability between multiple data-generating sources (i.e. practices) that was specifically designed and tested for multitype, multivariate and multimodal biomedical data.22,23 Where outlying practices are identified, analysis will be re-run without those practices and results presented with the analysis outlined in *N. Data/ Statistical Analysis*. |

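### Prior antibiotic use and prior infection consultations are named in no covariate list or model, although the rationale rests on the most frequent antibiotic users

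*Protocol*

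**What the plan says.** The rationale (Protocol, Objectives, Specific Aims and Rationale) starts from the finding that "more than half of all antibiotic prescriptions in primary care are issued to less than 10% of patients". It names as its underlying assumption that "it might be safe and feasible to reduce prescribing in patients with the highest levels of antibiotic prescribing, many of whom have co-morbidity". Study Background repeats the target: "reductions in antibiotic resistance may require targeted public health interventions aimed at reducing antibiotic prescribing for patients who have the highest frequency antibiotic use".

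The comparison actually planned is by co-morbidity, "comparing effects in patients with co-morbidity to those in controls without co-morbidity". The hypothesis in Study Type is that the "protective effect of antibiotics against adverse outcomes of infection differs between groups of patients with and without these risk factors", where the listed factors are age, gender, SES, co-morbidity, smoking and obesity.

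Step 4 of section N estimates the antibiotic effect by logistic regression, "adjusting for age, gender, SES, ethnicity, year/season, co-morbidity and the probability of receiving antibiotic treatment", with interactions for age and co-morbidity and random effects for practice and patient. Section O describes the propensity inputs as indicators of severity and of "risk of complication, such as prior hospitalisation and immunosuppression". It adds GP prescribing preference as an instrument, because severity is poorly recorded. The Amendments add cardiovascular disease, liver disease, immunosuppression and the Charlson index.

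**The concern.** A patient who has often consulted for infection and often received antibiotics is plausibly more likely both to be prescribed one at the next consultation and to come back within 28 days. If so, prescribing and consulting history confounds the effect on re-consultation. That outcome is one of the two that section O names for the NNT, and it is part of the step 5 composite. The bias would make antibiotics look less protective, or harmful.

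History is also the characteristic by which the rationale defines its target group. No analysis is planned of whether the antibiotic effect differs by level of prior use. Whether prescribing can safely be reduced in the highest users is therefore approached only through co-morbidity, which by the protocol's own account many of them have, not all.

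**Working it through.** **1. Where history could enter, and whether it is named**

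- Section M, covariates: age, sex, deprivation, four co-morbidities, obesity, smoking, season and year, ethnicity. History is not named.
- Section N, models of steps 1, 3 and 4: not named. Interactions with treatment in step 4 are age and co-morbidity only.
- Section N, step 2: a prescription count per patient is calculated, but it is descriptive. It covers the whole study period, so it includes prescriptions after an index date and cannot serve as a pre-index covariate.
- Section N, step 5, candidate predictors: socio-demographic factors, co-morbidity and clinical presentation. Not named.
- Section O, propensity score: an open list with two examples, neither of them history.
- Amendments: the covariate list was reopened to avoid biased results, and history was not added.

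**2. Whether the planned safeguards cover it**

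- A patient random intercept accounts for correlation between episodes. It assumes that the patient effect is independent of treatment, so it does not remove confounding by a patient's tendency to receive antibiotics and to return.
- The propensity inputs are directed at severity and complication risk, not at consulting behaviour.
- Section O itself lists patients' attitude to antibiotics among the influences on prescribing. Past courses and attendances are recorded markers of it.
- Section K lets patients enter a syndrome cohort repeatedly, so frequent consulters contribute many index episodes.

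**3. Possible size on re-consultation**

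The protocol states no figure to reproduce, and every input here is an assumption. Let h be the share of episodes in high prior users, q their probability of a prescription and r their re-consultation risk. Other patients are prescribed in 50% of episodes and re-consult in 8%. Antibiotics have no effect.

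Treated risk = [hq·r + (1−h)·0.5·0.08] / [hq + (1−h)·0.5]

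Untreated risk = [h(1−q)·r + (1−h)·0.5·0.08] / [h(1−q) + (1−h)·0.5]

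- Middle case (h = 20%, q = 70%, r = 20%): treated (0.14×0.20 + 0.40×0.08)/0.54 = 11.1%; untreated (0.06×0.20 + 0.40×0.08)/0.46 = 9.6%. OR 1.18; 1/0.0155 gives a false number needed to harm of about 65.
- Low corner (10%, 60%, 16%): treated 0.0456/0.51 = 8.94%; untreated 0.0424/0.49 = 8.65%. OR 1.04, risk difference 0.3 points.
- High corner (30%, 80%, 25%): treated 0.088/0.59 = 14.9%; untreated 0.043/0.41 = 10.5%. OR 1.50, risk difference 4.4 points.

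**4. Cross-check at the protocol's planning values**

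Section I uses an OR of 0.69 and a risk of 2.4%. Taking 2.4% as the untreated risk, the treated risk is 0.024×0.69/(0.976 + 0.024×0.69) = 1.67%, a true NNT of 137. The bias factor is [1 + a(RR−1)]/[1 + b(RR−1)], where a and b are the assumed shares of frequent users among treated and untreated episodes, and RR is their relative outcome risk.

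- a = 15%, b = 10%, RR 1.5: 1.075/1.05 = 1.024; OR 0.71, NNT 144.
- a = 30%, b = 20%, RR 2: 1.3/1.2 = 1.083; OR 0.75, NNT 168.
- a = 30%, b = 10%, RR 3: 1.6/1.2 = 1.333; OR 0.92, NNT 533.

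The bias runs from negligible to large, and the protocol gives no inputs to narrow it.

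**The case against.** Four things can be said on the other side.

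First, the propensity list is open, and its full content is commonly left to a statistical analysis plan, which is not at hand. This stands to the extent that one cannot say the two histories enter no model, only that none names them. It does not dispose of the point: section M gives a definite list of covariates, and the propensity inputs are described by a purpose that does not cover consulting history.

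Second, the formal aims, hypothesis and comparison groups concern age, co-morbidity, smoking, obesity and similar factors. A reader might infer that the study cannot answer its own question. The documents do not support that. The plan addresses the groups it sets out to compare, and high use is the motivation. What remains is a mismatch between rationale and analysis.

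Third, the arithmetic is crude. It precedes all adjustment, and co-morbidity, prior hospitalisation and the GP-preference instrument may absorb part of the bias. Section O already expects confounding in this direction. This stands: the figures illustrate confounding before adjustment, not the bias left in the planned analysis. It would also be tempting to set them against the OR of 0.975 that section I says is detectable, but that figure belongs to an outcome risk of about 2.4%, while the re-consultation illustration uses 8% to 25%.

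Fourth, the remedy is not free. Step 1 extracts events within the study period only, so history before April 2007 is not in hand. For patients who re-enter, earlier consultations can be earlier outcomes, and entering them beside a patient random effect can itself bias estimates. Prior prescriptions also partly reflect GP preference, the planned instrument. These objections bear on how history is entered, not on whether it should be named.

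**Conclusion.** The point holds in a limited form. Prior prescriptions and prior infection consultations are named nowhere as covariates, propensity inputs or effect modifiers, while the rationale rests on the highest users. The step 4 effect on re-consultation may therefore be biased towards harm, and the premise about the highest users is tested only by proxy.

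That frequent users do confound the effect is plausible but not shown. The range of OR 1.04 to 1.50 rests wholly on assumed shares, prescribing probabilities and risks, no true effect, and no other adjustment. It concerns re-consultation only. A reader might also infer that the bias is worst in co-morbid groups; nothing in the protocol or in this check establishes that. The gap is worth closing because the change is modest and bears on a main outcome.

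**What to change.** Add to section M two covariates measured in the 12 months before each index date: the number of antibiotic prescriptions and the number of infection consultations. Name both as inputs to the propensity score used in step 4. As a secondary analysis, report the antibiotic effect and NNT by prior-use category (for example 0, 1–2, 3 or more). If that analysis is not wanted, narrow the rationale to co-morbidity groups.

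The cost is two derived variables, some wording and one secondary analysis, with three conditions:

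- Infants have a shorter look-back and need their own category.
- Index episodes before April 2008 need records from before April 2007, or must be left out of this analysis. Section K requires a year's registration before entry (infants excepted), but step 1 does not extract that year for patients entering at the study start.
- Because patients re-enter the cohorts, history is best entered through the propensity score rather than as lagged terms in the outcome model, with a sensitivity analysis on each patient's first episode.
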